### Procedure

In phase 1, following the initial eligibility screening and identification as possible participants, interested individuals will be contacted by emails or phone to invite them to schedule a 1-hour mock consent session with a member of the study team. Before the mock consent session, participants at UNC will e-sign an Web-based consent form sent by Qualtrics and those at MUSC provide verbal consent at the time of scheduling, which is confirmed by the coinvestigator prior to participating in study procedures. During the mock consent session, study personnel will give participants a brief overview of Doxy.me and teleconsent before walking participants through a mock consent form created for this study. The purpose of the mock consent form is not to actually complete an informed consent session but to highlight the functionalities of the software. Immediately after the completion of the mock consent process, study personnel will conduct audiorecorded, semistructured interviews with participants about their experiences. After the study completion, participants will either receive cash or a gift card sent electronically or mailed to their residence(s). In total, 40 participants are to complete phase 1 of the study at each site, for a total of 80 participants between UNC and MUSC.

For phase 2, participants (n=64 at each site) will be assigned to either consenting for the clinical trial through teleconsent (n=32) or through paper-based consenting (n=32). Notably, 64 subjects per site (totaling n=128 between sites) will provide 80% power to detect modest differences (effect sizes ~0.50) between groups with respect to the survey instrument scores. After consenting for participation in the teleconsent study, participants will undergo the informed consent process using either teleconsent or traditional consent. After the completion of the consent process, participants will immediately fill out the quality of informed consent (QuIC), Decision-Making Control Instrument (DMCI, and Short Assessment of Health Literacy-English version (SAHL-E). Thirty days postconsent, participants will be asked to fill out this set of surveys once more electronically; they will be paid for each set of surveys completed.

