### Data Analysis

In phase 1, all interviews will be professionally transcribed and imported into the NVivo 12.0 (QSR International Pty, Doncaster, VIC, Australia) qualitative analysis software. Verification of the transcript accuracy will be performed prior to analyzing the text. An iterative process will be used in the analysis of the data. Then, 2 team members will code the data following its transcription by tagging segments of text in the transcripts to a concept, expanding, refining, and reducing the concepts, and discussing the findings in detail to allow for cross-validation of findings between the 2 sites [28]. A coinvestigator at MUSC with advanced training in research ethics and bioethics will explore the ethical appropriateness and associated principles of teleconsent using an integrative bioethical approach, and the MUSC research team will review emerging findings at the midpoint and conclusion of coding to consider what additional data will be necessary to refine our understanding of the participants’ perspectives related to teleconsent and determine overall themes. In addition, any feedback about the Doxy.me software will be submitted to developers at MUSC.

In phase 2, for patient participants, descriptive statistics (means, SDs, medians, etc) of responses to the survey instruments will be used to characterize the 2 groups (ie, teleconsent vs paper-based consent). Participants will be stratified with respect to demographics and clinical study. Each of the survey instrument summary scores and subscale scores will be essentially continuous variables; as such, comparisons between groups will be delineated through analysis of covariance modeling. In these models, the instrument score will serve as the dependent variable, with the experimental group serving as the key independent variable of interest. The analysis of covariance model includes participant factors, such as education and other demographics, as covariates in the models.

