In phase 1 of this study, participants will be recruited; participants will be residents of South and North Carolina (N=80; 40 from each respective site) from various backgrounds; however, all will meet the inclusion criteria specific to this study. Participants will be walked through the teleconsent process using a mock consent form and then interviewed to determine the overall themes regarding issues such as software difficulties and privacy issues. Results from this part of the study will be used to provide feedback to developers at the MUSC and address potential issues before phase 2, which will be completed in the summer of 2019. In addition, it will provide data on participant preferences, acceptability, and potential barriers to the adoption of teleconsent. For phase 2, researchers partner with ongoing clinical trials and assign participants (n=64 at each site) to either consenting by teleconsent or traditional paper-based consenting. Various validated surveys will be given to participants both immediately after the consent process and 30 days postconsent to determine differences in the understanding of the consent process between groups. Moreover, surveys will be administered to the study personnel who are consenting patients throughout the process to study the additional workload and demand placed upon them. We hypothesize that there will be no significant difference in the quality of informed consent or additional workload demand placed on researchers between traditional paper-based consenting and teleconsent. With these results, we hope to increase the usage of teleconsent in clinical trials to reduce barriers to study enrollment and improve underserved groups’ participation in research.

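### QuIC and DMCI are scored twice per phase 2 participant, but the stated ANCOVA makes no provision for time; a repeated-measures model with a named primary time point is a cheap improvement

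*Protocol article*

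**What the plan says.** All references are to the protocol article.

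- **Two assessments per person.** Under Procedure, the first set of surveys follows consent directly: "After the completion of the consent process, participants will immediately fill out the quality of informed consent (QuIC"), together with the DMCI and a health-literacy test. Then: "Thirty days postconsent, participants will be asked to fill out this set of surveys once more electronically".
- **Both are used to compare arms.** The Discussion says that surveys are given "both immediately after the consent process and 30 days postconsent to determine differences in the understanding of the consent process between groups".
- **One model is named.** Under Data Analysis, "comparisons between groups will be delineated through analysis of covariance modeling". The outcome and main term follow: "In these models, the instrument score will serve as the dependent variable, with the experimental group serving as the key independent variable of interest". The other terms are participant characteristics: "The analysis of covariance model includes participant factors, such as education and other demographics, as covariates in the models".
- **Size.** Under Procedure, "participants (n=64 at each site) will be assigned to either consenting for the clinical trial through teleconsent (n=32) or through paper-based consenting (n=32"). That makes 128 over the two sites, or 64 per arm, for which the article claims 80% power at a standardized effect of about 0.50.

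The text does not say which occasion the score comes from, whether the two occasions share a model, or which is primary.

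**The concern.** The design yields two correlated scores per person, while the model as described is written for one score per person. It can be read in two ways.

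- **Both scores in one ANCOVA with no participant term.** Two scores from one person would count as independent, so the standard error of the arm contrast would be too small.
- **One ANCOVA per occasion.** Each test is sound with complete data. At 30 days, however, anyone who does not return the second survey drops out, and that person's immediate score is not used, although it carries information about the missing one.

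The arm comparison of comprehension and voluntariness is the main patient result of phase 2, and the authors expect to find no significant difference. Lost power at 30 days makes that outcome easier to reach; an understated standard error makes a spurious difference more likely.

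**Working it through.** **Inputs from the article.** 64 per arm (pooled sites), standardized effect d = 0.50 with SD 1, and two-sided alpha .05. The alpha is stated in the paragraph on study personnel and is assumed here to apply to patients. The QuIC test-retest coefficient of .77 is given under Study Instruments.

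**Assumed, because the article gives no figure.** The correlation rho between a person's two scores is .3, .5 or .77, the last borrowed from the test-retest coefficient. Non-return m at 30 days is 10%, 20% or 30%. Covariate adjustment is ignored.

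**Step 1: the article's own figure.** Power = Φ(d·√(n/2) − 1.96) = Φ(0.50·√32 − 1.96) = Φ(0.868) = 80.7% (noncentral t: 80.1%). The required size is 63 per arm. The stated 80% therefore reproduces for the pooled 128 with one score per participant, and it contains no allowance for non-return.

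**Step 2: if both scores were pooled without a participant term.** The mean of a person's two scores has variance (1 + rho)/2, while the model assumes 1/2. The variance of the arm contrast is understated by the factor 1 + rho, so the true error rate is 2·[1 − Φ(1.96/√(1 + rho))].

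- rho = .3: 1.96/1.140 = 1.719, rate 8.6%
- rho = .5: 1.96/1.225 = 1.600, rate 11.0%
- rho = .77: 1.96/1.330 = 1.473, rate 14.1%

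Simulation with 64 per arm and 20,000 runs gave 10.5% at rho = .5 and 14.5% at rho = .77.

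**Step 3: if each occasion has its own ANCOVA.** At 30 days the variance is multiplied by 1/(1 − m). In a joint model of both occasions it is multiplied by (1 − rho²)/(1 − m) + rho². With m = 0 both factors equal 1, so both analyses have 80.7% power.

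Example with m = .2 and rho = .77: the separate analysis has 64 × .8 = 51.2 per arm, giving Φ(0.50·√25.6 − 1.96) = 71.6%. The joint factor is .4071/.8 + .5929 = 1.102, an effective 58.1 per arm, giving 76.9%.

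| Non-return | Separate 30-day ANCOVA | Joint, rho .77 | Joint, rho .5 |
|---|---|---|---|
| 0% | 80.7% | 80.7% | 80.7% |
| 10% | 76.5% | 79.0% | 77.6% |
| 20% | 71.6% | 76.9% | 73.7% |
| 30% | 65.8% | 74.2% | 69.2% |

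The gain at rho = .77 is 2.5, 5.3 and 8.4 points; at rho = .5 it is 1.0, 2.2 and 3.4 points.

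**Step 4: bias at 30 days among returners only.** These are simulations with no true effect, 64 per arm and about 20% non-return.

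- Return depends on the first score in the same way in both arms: no bias, and rejection rates of 5.0% to 5.5%.
- Return depends on the first score in one arm only (logit slope 0.8 per SD): bias of 0.07 SD and 6.5% rejection at rho = .5; 0.13 SD and 9.4% at rho = .77.
- The same with slope 1: 0.09 SD and 7.3% at rho = .5; 0.14 SD and 10.8% at rho = .77.

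**Step 5: two tests per score.** Testing each occasion at .05 gives a chance of at least one false positive of 9.1% at rho = .5 and 8.0% at rho = .77, for each score.

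**The case against.** The strongest reply is that the article contains no false statement here. It is a condensed account, and how two occasions enter a model and how missing surveys are handled are usually settled in the full protocol or analysis plan. It speaks of models in the plural, its power statement uses one score per person, and its covariate list is given by way of example. One ANCOVA per occasion is thus at least as natural a reading as a pooled one, and it holds 5% for each test.

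The correlation is also borrowed: .77 is a reliability figure for the QuIC, not the correlation between the two planned occasions, and no such figure is given for the DMCI. Participants are paid for each completed set, which encourages return. Even at 20% non-return the joint model reaches only 76.9%, so most of the shortfall comes from non-return and not from the choice of model. Covariates could offset it: if they explained an assumed 20% of the variance, full-data power would be 88.5%.

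Most of this stands, and it limits the size of the point. A reader might infer that the planned analysis inflates the false-positive rate, or that a separate 30-day ANCOVA is in itself underpowered or biased. The documents support neither. No sentence says that the scores are pooled, the power loss appears only with non-return, and the bias needs return to depend on the first score differently by arm, which nothing in the article indicates.

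What the reply does not remove is that the article is not silent on method. It names the model, outcome, main term and type of covariate, and as described that model does not use the repeated measurement that the design collects.

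**Conclusion.** The point holds as an inexpensive improvement to a stated method, not as an error. If the occasions are analysed separately, as is natural, nothing is lost with complete data. With 10% to 30% non-return, the 30-day contrast gives up about 2.5 to 8 points of power against a joint model at correlation .77, and about 1 to 3 points at .5. It is also exposed to a bias of roughly 0.07 to 0.14 SD under the one-arm return scenarios above. The 9% to 14% false-positive rate applies only to a pooled analysis that the article does not describe; the wording should simply rule that out. The comparison immediately after consent is not affected by 30-day non-return. All these sizes rest on assumed return rates and correlations.

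**What to change.** In Data Analysis, replace the ANCOVA for each QuIC and DMCI score with one linear mixed model for repeated measures. Its terms are arm, time (immediate, 30 days), arm-by-time and the planned participant covariates, with an unstructured within-participant covariance. Include every participant with at least one score, report the arm contrast at each time, and name which time point is primary. State that the immediate score is not a covariate for the 30-day comparison: it is measured after the mode of consent has been applied and is itself an outcome.

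As a minimum, the text could state that a separate ANCOVA is run at each occasion and which one is primary. That settles the ambiguity but leaves the loss from non-return.

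The cost is a change of wording; no further data, participants or staff are needed, and the article describes phase 2 as still to start. The downside is reliance on data being missing at random given the immediate score, a weaker requirement than that of a 30-day analysis of returners only. The model reduces the power loss from non-return but does not eliminate it.

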**Figure 2 figure2:**
[figure not shown]
The teleconsent software allows the research coordinator and participant to sign the consent form in real time electronically.

For phase 2, participants will not be directly recruited for our study. Instead, we will partner with investigators conducting ongoing clinical research and assign those study participants to use either teleconsent or traditional paper-based consenting for the informed consent process. In total, 64 patients and up to 10 research assistants will be involved in this part of the study at the UNC site, though the number of research assistants may be as low as 2. Patients will be paid each time a set of surveys are completed. Research assistants will be paid upon the completion of each National Aeronautics and Space Administration (NASA)-Task Load Assessment (TLX) form (to be completed after each consent session) and also upon the completion of each System Usability Scale (SUS; to be completed approximately 3 times throughout the study). In addition, research assistants will be paid for participation in a focus group.

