Study personnel who are consenting potential participants will fill out a NASA-TLX form for each patient; they will be paid for each form filled. In addition, they will fill out SUS 3 times throughout the study, once at the beginning of their participation, once toward the middle, and once after they have completed enrolling participants for the teleconsent study; they will be paid for each SUS filled out. Finally, after the termination of the teleconsent partnership, those who will be obtaining informed consent for these studies and will assist in the collection of instruments will be invited to participate in a focus group asking about their workload and perceptions of the Doxy.me software for teleconsent. Focus group participants will be receiving remuneration for completing the focus group.

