For study personnel, descriptive statistics will be used to study the differences in the NASA-TLX between the 2 groups through a 2-sample *t* test of means. The sample size of the research assistant group will be based on the number of research assistants currently working on the clinical trials. Regardless, we will assume 2-sided hypothesis testing with an alpha level of.05. We suspect that the null hypothesis will display no significant difference in the means of the research assistants’ NASA-TLX scores for teleconsent versus paper-based consenting.

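### The NASA-TLX comparison uses an independent 2-sample t test on repeated ratings from a few research assistants, so its nominal .05 does not hold in general

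*Protocol article*

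**What the plan says.** Procedure (phase 2) fixes how the data arise: "Study personnel who are consenting potential participants will fill out a NASA-TLX form for each patient". Recruitment confirms the timing, "to be completed after each consent session". For UNC it plans on 64 patients and at most 10 assistants, with a caveat about the lower end: "though the number of research assistants may be as low as 2".

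Data Analysis then turns to workload and says that "descriptive statistics will be used to study the differences in the NASA-TLX between the 2 groups". The method it names is a comparison "between the 2 groups through a 2-sample *t* test of means". On the number of assistants it says: "The sample size of the research assistant group will be based on the number of research assistants currently working on the clinical trials". The error rate is set all the same, two-sided at .05. It mentions no term for the assistant, no pairing and no other allowance for repeated ratings. The Discussion hypothesizes no significant difference in workload between the two ways of consenting.

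**The concern.** NASA-TLX is a subjective rating, and people differ in how they use such a scale. Forms from one assistant will therefore resemble each other more than forms from different assistants. A 2-sample t test assumes that all observations are independent and that the two groups consist of different units. The data collection described in Procedure and Recruitment does not produce such data.

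The unit of analysis is also unclear, because Data Analysis ties the sample size to the number of assistants although the measurements are forms. Neither choice rescues the test:

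- **Form as unit:** forms are correlated within assistant.
- **Assistant as unit, both modes used:** the two sets of means come from the same people and are paired.
- **Assistant as unit, one mode each:** there may be as few as 1 assistant per mode, and no t test is possible.

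This is the only hypothesis test planned for workload. A test that is too conservative leans towards the result the authors expect. A test that is too liberal can report a difference between people as a difference between consent modes.

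**Working it through.** **The plan's own figure.** The article states 80% power at an effect size of about 0.50 with 128 patients. It reproduces: 64 per arm gives 80.1% for a two-sided t test at .05. It concerns patient survey scores and independent observations, so it does not support the NASA-TLX comparison, for which no power is stated.

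**Inputs from the article.** One form per patient, 64 patients per site, 32 per mode, two-sided alpha .05, and 2 to 10 assistants at UNC, which is 64/10 = 6.4 to 64/2 = 32 forms each.

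**Assumed inputs.** The article gives no intraclass correlation (ICC), written ρ, for assistants. The range 0.05 to 0.5 is used. Total variance is set to 1, with n = 32 forms per mode and k assistants.

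**Split layout (each assistant works in one mode; h = k/2 per mode).**
- True variance of the mean difference: 2[ρ/h + (1−ρ)/n].
- Variance the t test uses, on average: 2[(1−ρ) + ρ(n/h)(h−1)/(n−1)]/n.
- For k = 2 and ρ = 0.3: 2(0.3 + 0.7/32) = 0.644 against 2(0.7)/32 = 0.0438. The true SE is √(0.644/0.0438) = 3.84 times the one used. The critical value 1.999 then acts like 1.999/3.84 = 0.52, a two-sided error of 0.60.

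**Crossed layout (each assistant uses both modes evenly, same mode effect for all).**
- True variance: 2(1−ρ)/n. Variance used: 2[(1−ρ) + ρ(n/k)(k−1)/(n−1)]/n.
- At ρ = 0.3 the SE used is too wide by a factor of 1.11, 1.15 and 1.18 for k = 2, 4 and 10.
- Power at d = 0.5, ρ = 0.3: with assistant differences removed, 0.5/√0.0438 = 2.39 and Φ(2.39 − 2.00) = 0.65. By simulation the t test gives about 0.58, 0.53 and 0.52 for k = 2, 4 and 10.

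**Crossed, with assistants differing in their response to mode.** The variance of an assistant's own mode difference is assumed to be 0.2 (a share of 0.10 within each mode). For k = 2 and ρ = 0.3 the true variance is 0.2/2 + 2(0.6)/32 = 0.1375, while the test uses 0.0504. The SE ratio is 1.65 and the error about 0.23.

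**Simulated type I error** (20,000 runs per cell, 64 forms, nominal .05, lowest to highest over ρ = 0.05 to 0.5):

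| Assistants | Split by mode | Crossed evenly | Crossed, response differs |
|---|---|---|---|
| 2 | 0.22–0.73 | 0.028–0.044 | 0.22–0.27 |
| 4 | 0.14–0.56 | 0.016–0.044 | 0.12–0.14 |
| 10 | 0.08–0.33 | 0.010–0.047 | 0.03–0.07 |

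With 128 forms from a total of 2, 4 or 10 assistants, the split layout gives 0.12 to 0.80 and the even crossed layout 0.009 to 0.046. The pooled number of assistants is unknown, because none is given for MUSC.

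**Assistant means as the unit, both modes used.** With 2, 5 or 10 assistants and an assumed correlation of 0.3 to 0.7 between an assistant's two means, the unpaired test has true size 0.002 to 0.038. A paired test on the same means has 0.048 to 0.051.

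**The case against.** A reader might infer that false positives rise several-fold. The large figures need assistants who each work in one mode, and the article does not establish that. It assigns patients, not assistants, to a mode. Procedure has the consenting personnel, without distinction by mode, complete the SUS three times and invites them to a focus group on the teleconsent software. Crossed is the more natural reading, and without differing responses to mode it gives a conservative test with a moderate loss of power. A split, at least in part, remains possible because Randomization allows parent studies in which some participants have no traditional option.

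Other strong readings also fail:

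- Inflation in the crossed layout with differing responses is marked with 2 assistants, but the error is near nominal with 10.
- Two assistants leave zero degrees of freedom only if they are split 1 against 1. Two crossed assistants give 2 against 2 means and hence 2 degrees of freedom, although wrongly unpaired.
- The range of 2 to 10 is stated for UNC and cannot be carried over to MUSC.
- It would be wrong to say that the third objective cannot be answered. Usability rests on the SUS, and the focus group covers both workload and perceptions.

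It might also be said that the detail belongs in an analysis plan not shown. That does not help, because the article itself names the test.

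What stands is that no layout consistent with the text yields the independent observations the test requires.

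**Conclusion.** The point holds as a mismatch between the stated test and the stated data collection. The true error rate of the workload comparison is not the nominal .05 in general, and its direction cannot be known from the article. With 64 forms and an assumed ICC of 0.05 to 0.5:

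- **Both modes used evenly:** about 0.01 to 0.05. At ICC 0.3, power at d = 0.5 is about 0.52 to 0.58 instead of 0.65, which favours the hypothesized result.
- **Assistants split by mode:** about 0.08 to 0.73.
- **Both modes used, responses differing (assumed variance 0.2):** about 0.2 to 0.3 with 2 assistants, near nominal with 10.

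The sizes rest on the assumed ICC and variance. The mismatch does not. It is confined to the quantitative workload comparison.

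**What to change.** 1. Record an assistant ID and a session number on every NASA-TLX form before phase 2 starts. Without the ID the correction may not be recoverable.
2. State the unit of analysis and whether assistants use both modes. Have them do so where the parent study allows; Randomization implies that this will not always be possible.
3. Replace the t test with a linear mixed model on all forms: fixed effects for consent mode, site or parent study, and session order; a random effect for assistant, with assistant-by-mode where it can be estimated; small-sample degrees of freedom. A paired analysis of assistant means is a simpler alternative. Report the mode difference with a 95% CI.
4. With very few assistants, estimate the within-assistant difference and limit the conclusion to those assistants. A fixed assistant effect does not control error across assistants when they differ in response to mode: under the assumed variance of 0.2 its type I error is about 0.27 with 2 assistants and 0.16 with 4. A paired test on 2 assistants has only 1 degree of freedom.
5. If assistants are split by mode with only 1 or 2 per mode, report the comparison descriptively.

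The cost is a change of wording, two extra data fields and a scheduling constraint, small where the parent study offers both modes.

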### Randomization

No randomization will be involved in phase 1. For phase 2, if the parent study permits, participants will be either randomly assigned to each of teleconsent or traditional consent. When random assignment is not possible, for example, in studies in which some participants do not have the option of being assigned to traditional consent, thereby negating random assignment, we will use the propensity score matching after assignment to either teleconsent or traditional consent. Once verbally consented through one of these means, participants will undergo the informed consent process.

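### The NASA-TLX comparison is set as an unadjusted t test, and the plan does not say whether its matching, covariates or stratification by clinical study apply, although consent mode may be non-random

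*Protocol article*

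**What the plan says.** All references are to the protocol article.

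- **Data Analysis, study personnel.** The plan is that "descriptive statistics will be used to study the differences in the NASA-TLX between the 2 groups" by a 2-sample t test, and "we will assume 2-sided hypothesis testing with an alpha level of.05". No covariate, matched set or parent-study term is named.
- **Data Analysis, patient participants.** The preceding paragraphs, introduced as applying to patients, plan an analysis of covariance: "The analysis of covariance model includes participant factors, such as education and other demographics". They also plan stratification by demographics and clinical study.
- **Randomization.** "For phase 2, if the parent study permits, participants will be either randomly assigned to each of teleconsent or traditional consent". The exception follows: "in studies in which some participants do not have the option of being assigned to traditional consent, thereby negating random assignment". Propensity score matching is then planned. The outcomes it serves are not listed.
- **Procedure.** Personnel "will fill out a NASA-TLX form for each patient". Each score therefore belongs to one patient and one parent study.
- **Timeline.** Two parent trials have been identified.
- **Need for This Research, and Discussion.** Workload is the third objective, and the hypothesis is no additional demand from teleconsent.

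**The concern.** How demanding a consent session is can depend on the patient (age, education) and on the parent study (length and difficulty of its consent form) as well as on the mode. The article gives reasons to expect this. Under Study Instruments it links lower education and advanced age to poorer comprehension, and in the Introduction it reports an inverse relation between age and satisfaction with teleconsent.

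The plan adjusts patient scores for such factors but names nothing comparable for workload. Where consent mode is not randomized, the arms can differ in parent studies and in patients. A 2-sample t test then reports the mode effect plus that difference. The bias can run either way: it can produce an apparent workload penalty, or hide a real one and seem to confirm the hypothesis.

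This is a separate matter from repeated forms by the same assistant. Even a single, fully practised assistant would give a confounded comparison if the modes had different study mixes.

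**Working it through.** **1. The plan's own figure.** Procedure claims 80% power at an effect size of about 0.50 for the survey scores. With 64 per arm (both sites pooled), the noncentral t gives 0.801, so the figure reproduces. No sample-size statement is made for NASA-TLX. I use 64 v 64 forms below because that is one form per patient over both sites.

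**2. Assumed inputs, not in the article.** There are two parent studies, A and B. Mean NASA-TLX in B is higher by D within-study SDs. The true mode effect is zero and forms are independent. B supplies a share pT of teleconsent sessions and pP of paper sessions.

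**3. Formulas.**

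- Bias of the unadjusted difference = D × (pT − pP).
- SE used by the t test ≈ √[(1 + D²·pT(1−pT))/64 + (1 + D²·pP(1−pP))/64].

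**4. One case by hand.** Take D = 0.5, pT = 0.5, pP = 0.

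- Bias = 0.5 × 0.5 = 0.25 SD.
- SE = √[(1.0625 + 1)/64] = 0.180.
- The critical difference is 1.979 × 0.180 ≈ 0.355. With the mix held fixed, the sampling SD of the difference is √(2/64) = 0.177.
- P(reject) ≈ P[Z > (0.355 − 0.25)/0.177] = P(Z > 0.595) ≈ 0.28.

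**5. Simulation.** Each row has at least 20,000 runs with 64 v 64 forms. Entries are the two-sided false-positive rates of the t test.

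| Share of B, teleconsent v paper | Bias | D = 0.3 | D = 0.5 |
|---|---|---|---|
| 50% v 50% | 0 | 5% | 4% |
| 62.5% v 37.5% | 0.25 D | 7% | 10% |
| 50% v 25% | 0.25 D | 7% | 10–11% |
| 75% v 25% | 0.5 D | 13% | 27% |
| 50% v 0% | 0.5 D | 13% | 28% |

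With one site only (32 v 32), the three unequal mixes simulated (62.5% v 37.5%, 75% v 25%, 50% v 0%) give about 6% to 16%. Adding a parent-study term brought the bias to about 0 and the rate to about 5% in every mix to which it was fitted (all rows but 50% v 25%).

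**6. What adjustment costs.** In the 50% v 0% case, study B has no paper sessions, so its 32 teleconsent forms say nothing about mode once study is in the model. The contrast becomes 32 v 64:

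- SE = √(1/32 + 1/64) = 0.217, against √(2/64) = 0.177, a rise of 22%.
- Power at 0.5 SD falls from 80% to 63% (noncentral t).

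In the 62.5% v 37.5% mix the SE rises only to 0.183.

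**The case against.** **Matching may already cover workload.** The matching is described in the Randomization section and is not limited to patient scores. Since each form belongs to a patient, the t test could be run on the matched set. This stands. A reader might infer that the plan excludes matching for NASA-TLX, but the text does not say so. It is silent, and that silence is the point. Even on a matched set, the test as named has no parent-study term and no covariates.

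**Random assignment is the first option.** With an even split in each parent study there is no inflation (4% to 5% in the table). This also stands. The stratification by clinical study might even be meant to govern assignment, which would balance the arms, although it appears in the patient analysis. The concern applies only to the case that the Randomization section itself foresees, "When random assignment is not possible, for example, in studies in which some participants do not have the option of being assigned to traditional consent".

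**The 28% is an extreme case.** It needs a study with no paper sessions supplying half the teleconsent arm, and a 0.5 SD difference between studies. The article speaks of some participants lacking the traditional option, not all. A reader should not take 28% as this trial's error rate, because neither the mix nor the difference can be learned from the article.

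**Adjustment need not improve precision.** Correct, as step 6 shows. Nor would study and patient covariates be enough alone. The Recruitment section allows as few as 2 and up to 10 assistants at the UNC site, so each may complete many forms, and the rates above ignore that dependence.

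**An article may leave covariates to the full plan.** True in general. Here the article names the test for workload and, beside it, a different, adjusted method for patients, so the choice is stated rather than omitted.

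**Conclusion.** The concern holds in a conditional form. The article names an unadjusted test for an outcome measured per patient and per parent study, allows non-random consent mode, and does not say whether its own safeguards extend to that outcome. Where the mix of parent studies or patients differs between modes, the comparison is confounded. Under assumed study differences of 0.3 to 0.5 SD, unequal mixes and 64 v 64 independent forms, the false-positive rate is about 7% to 28% instead of 5%. If every parent study randomizes evenly, it is not inflated.

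The documents do not support the stronger conclusion that the workload comparison will be biased whatever happens. That depends on how the partner trials assign consent mode, which the article leaves open. The change is worth making because it is cheap and protects one of three stated objectives.

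**What to change.** In Data Analysis, study personnel:

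1. Replace the t test by a linear model of the per-session NASA-TLX score on consent mode, with parent study and the patient's age and education as covariates and a research-assistant effect. If each assistant works in only one parent study, say how the assistant and study terms will be handled, because they then overlap.
2. Link each NASA-TLX form to its patient by an identifier, if this is not already done.
3. State that the matched set from the Randomization section also applies to NASA-TLX for parent studies without random assignment.
4. Report two sensitivity analyses: the randomized parent studies alone, and additional adjustment for SAHL-E. The first is not suited to be the main estimate, since only two trials are foreseen and it might leave one or none. SAHL-E is completed after consent, so it should not be a core covariate.

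**Cost.** This needs analysis wording and at most an identifier on the form. Education and demographics are already in the patient analysis. The statistical cost is a loss of precision if a parent study uses one mode only, because its sessions then carry no information on mode. In the most unequal mix above, the SE rises from about 0.18 to 0.22 SD.
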